## Materials and methods

### Study design and setting

This trial is designed as a single-blinded two-arm randomized controlled trial (RCT) with parallel groups, and an allocation ratio of 1:1. Fig 1 illustrates the overall study. This study protocol follows the SPIRIT Statement guidelines for standard protocol items in clinical trials [46] and is registered in the Clinicaltrials.gov ID: NCT04868240 (date of registration April 30, 2021). This RCT study has been designed and results will be reported according to the Consolidated Standards of Reporting Trials (CONSORT) statement [47]. Furthermore, and since that exercise training interventions are not properly and completely addressed by the CONSORT checklist [48], the guidelines of the Consensus on Exercise Reporting Template (CERT) will also be considered [49].

**Fig 1 pone.0263455.g001:**
[figure not shown]
Study design diagram.

### Participants

In this RCT, a minimum of 40 office-workers aged 40–64 years will be recruited, enrolled, and randomized (n = 20 per group). Potential eligible subjects will be recruited from two office companies in Coimbra city, Portugal. The principal investigator (PI) of this project will meet with the directors/leaders of these companies to present and discuss the purposes and procedures of this research project. Afterwards, a poster will be disseminated on their internal web pages and the subjects will be able sign up online or by telephone. Interested subjects will receive information about the study and will be pre-screening for initial eligibility criteria through telephone/online interviews. The subjects ruled eligible will be invited for an in-person screening visit where they learned more about the study, sign the informed consent form, and complete additional screening measures. Lastly, the subjects that meet all the defined eligibility criteria will be invited to return for a baseline assessment visit. After the baseline assessments, participants will be randomized and notified by email/telephone (by the PI).

Participant inclusion and exclusion criteria are presented in Table 1. These criteria are conceived to recruit healthy but physically inactive adults, with occupational jobs characterized by low levels of PA and high levels of SB and exclude adults with poor health or physically active. The term “physically inactive” refers to adults who do not achieve the recommended levels of moderate to vigorous PA outlined in the “WHO—Global recommendations on physical activity for health” [50]. These recommendations include the weekly accumulation of at least 150 minutes of moderate-intensity aerobic activity or 75 minutes of vigorous-intensity aerobic activity, and muscle-strengthening activities at moderate or vigorous-intensity on two or more days per week [50, 51]. The protocol of this study has been approved by the Ethical Committee for Health of the Faculty of Sport Sciences and Physical Education of the University of Coimbra (reference: CE/FCDEF-UC/00512019; approved on June 09, 2021). All procedures will be conducted in accordance with the Declaration of Helsinki [52] as well as with data protection and security regulations [53]. Study procedures, potential risks and expected results will be explained to the participants that will also hear of the voluntary character of their participation in this study, and of their right to withdraw without any prejudice or consequence.

**Table 1 pone.0263455.t001:** Inclusion and exclusion criteria for participants.

**Inclusion Criteria**
Men and women between 40 to 64 years old
Physically inactive adults (not meeting the Global recommendations on physical activity for health [50, 51])
Full-time workers with sedentary occupations (report spend ≥65% of their workday in activities with low energy expenditure i.e., 1.5 METs or lower);
Body mass index between 18 and 29.9 kg/m^2^
Willingness to maintain the current nutrition pattern and to participate in all testing assessments
**Exclusion Criteria**
Diagnosis of chronic disease (e.g., diabetes mellitus, cardiovascular and pulmonary diseases)
Cognitive or psychiatric conditions that need chronic treatment (e.g., depressive disorder) and that in the investigators’ opinion could interfere with the study outcomes
Take any regular medication that in the investigators’ opinion could interfere with the study outcomes
Limitations that prevent them from practicing exercise
History of heart failure and/or myocardial infarction
Uncontrolled or abnormal blood pressure
Participation in any intervention trial within 6 months prior to screening
Current participation in another intervention trial
Smoking
Failure to provide consent

### Randomization

Participants who meet all eligibility criteria will be randomly assigned to either control or experimental group with a 1:1 allocation as per a computer random number generator. Permuted block randomization will be used to ensure an equal sample size in the two groups. The block sizes will not be divulged to ensure concealment. This randomization process will be generated by an independent biostatistician. The study participants will be enrolled and assigned to their respective groups by the PI. The experimental group will perform 16-weeks of CT exercise and the control group will maintain their usual habits, including not participating in any exercise program.

### Estimated sample size

The sample size was calculated using a priori power analysis through the G*Power software version (3.1.9.2.), following the guidelines of Faul et al. [54]. For an effect size of 0.30, a sample size of 20 participants per group achieves 95% power to detect differences among the means versus the alternative of equal means using an F test with a 5% α-level. This analysis indicated a minimum total sample size required in this study. We plan to enrol 20% more persons to account for dropouts.

### Exercise intervention

The exercise program will be conducted following the American College of Sports Medicine (ACSM) recommendations [29, 55]. The exercise sessions will occur 3 times/week (i.e., Monday, Wednesday, and Friday) during approximately 75 min/session over 16 weeks (achieving 225 min/week, meeting public health guidelines for middle-aged adults), in an enclosed gymnastic pavilion. All exercise sessions will be conducted and supervised by two instructors who graduated in Sport Sciences with wide experience in the area. The two instructors are also responsible for encouraging participants to complete the exercise sessions/program, provide feedback, and assure the correction and safety of exercise execution. Before starting the exercise program, subjects will be submitted to estimated maximal dynamic strength tests aiming at setting their workload (i.e., 10 repetitions maximum (RM) protocol) [56].

Each session will consist of a warm-up (10 min), the main part of the session (aerobic plus resistance exercise) (60 min), and a return to calm (5 min). In the warm-up, the participants will perform 10 minutes of light-to-moderate intensity cardiorespiratory and muscular endurance activities to increase muscle temperature and promote an adequate cardiovascular response for CT exercise [55]. The main part of the session will be divided into two phases. In phase 1, participants will perform eight resistance exercises, that involve the use of body weight and free weights, namely: chest press, lateral arm raises, bent-over two-arm row, push-ups (incline or flat), front squat, deadlift, calf raises, and abdominal exercises (e.g., planks with knee and elbows or knees and toes). The participants will perform 1–2 sets of 6–15 repetitions with a 2–3 min rest interval between sets and exercises. For free weights exercises, the load will be adjusted individually to work between 45–90% of the estimated 1-repetition maximum (1RM), following a gradual progression in intensity throughout the weeks (see Table 2) [55]. The constant load method and the progressive load method will be used in the program. Participants will be instructed to inhale and exhale during the eccentric phase and concentric phase, respectively, while maintaining a fixed cadence of movement at a ratio of 2:2 s [55]. Maximal dynamic strength will be re-evaluated after 8 weeks (mid-testing) using 10RM protocol to guarantee those exercise prescriptions are continuously updated. In phase 2, participants will perform aerobic exercises (e.g., fast walking, running) with intensity based on predicting heart rate reserve (HRR). Aerobic exercise prescriptions will be based on 60%-95% of HRR following a gradual progression in intensity throughout the weeks that can be continuous, interval, or varied continuous (Table 2). Resting heart rate (HR) will be reassessed every 4 weeks so that HRR prescriptions can be continuously updated throughout the CT program. The participants will also be asked to rate their perceived effort levels on the Borg CR-10 scale to ensure that they are exercising at the planned intensity. In the last 5 minutes of the session, a cool-down period involving aerobic activities of light intensity, relaxation, and static stretching movements of the large muscle groups (10–15 seconds in each position and 1–2 repetitions) will be performed to allow for a gradual recovery of HR and blood pressure (BP) [55].

**Table 2 pone.0263455.t002:** Overview of the exercise program.

Group	Frequency and duration	Intensity				Types
		(Week 1–4)	(Week 5–8)	(Week 9–12)	(Week 13–16)	
Combined Training Group	3 times per week (Monday, Wednesday, and Friday) Main part of the session: 60 min (30 min aerobic plus 30 min resistance)	Resistance exercises: 1–2 sets of 10–15 reps at 45%-65% 1RM; and RPE of 5–6 on the Borg CR-10 scale (from 0 = extremely easy to 10 = extremely hard).	Resistance exercises: 2 sets of 10–12 reps at 60%-75% 1RM; and RPE of 5–6 on the Borg CR-10 scale.	Resistance exercises: 2 sets of 8–12 reps at 70%-85% 1RM; and RPE of 6–7 on the Borg CR-10 scale.	Resistance exercises: 2 sets of 6–12 reps at 75%-90% 1RM; and RPE of 7–8 on the Borg CR-10 scale.	Loading methods: constant and progressive. Examples: Chest press, lateral arm raises, bent-over two-arm row, push-ups, front squat, deadlift, calf raises, abdominal exercises.
		Aerobic exercises: 60%-75% of maximum HRR; and RPE of 5–6 on the Borg CR-10 scale.	Aerobic exercises: 70%-85% of maximum HRR; and RPE of 5–6 on the Borg CR-10 scale.	Aerobic exercises: 80%-90% of maximum HRR; and RPE of 6–7 on the Borg CR-10 scale.	Aerobic exercises: 80%-95% of maximum HRR; and RPE of 7–8 on the Borg CR-10 scale.	Exercise continuous, interval or varied continuous. Examples: fast walking, running, stepping, circuit training.
Control Group		No exercise training				

Notes: min, minutes; HRR, heart rate reserve; reps, repetitions; RPE, rate of perceived exertion; 1 RM, 1-repetition maximum.

Participants from both groups will be encouraged to conduct their daily activities as usual outside of the study and to maintain the same nutritional pattern/diet. The participants may not participate in any other exercise program. For ethical reasons and to avoid possible dropouts [48] during the study period, the control group will also receive the exercise intervention after having served as a control group.

#### Program attendance/adherence

The exercise program will last for a total of 16 weeks, with a total of 48 exercise sessions. The percentage of adherence to the exercise sessions will be calculated individually through the total sum of sessions participation. Participants of the CT group will be invited to participate in all training sessions and only those who have an adherence of ≥ 80% will be integrated into the analysis (i.e., attends 38 of the 48 exercise sessions) [57, 58]. Attendance at sessions will be recorded and entered on a database. Strategies to promote exercise adherence will include texts and email support as suggested by Connelly et al. [59]. If the participant has two consecutive absences, he or she will be contacted to return to the physical exercise sessions, since the lack of adherence may impair obtaining the desired intervention effects [60].

#### Exercise intensity control

Heart rate monitors (Polar V800^®^, Polar Electro Oy, Finland) will be used during all sessions to assess, monitor, and adjust the intensity of the HR interval of the participants. As a preventive measure, the exercise intensity will be indirectly predicted applying Karvonen’s formula to predict target HR [61]:

TargetHR=((MaximumHR–RestingHR)%intensity)+RestingHR))

Maximum HR (HR_max_) will be calculated using the equation formula proposed by Gellish et al. [62]:

HRmax=((207–(0.7xage))

For resistance exercises with free weights, the load will be adjusted individually through an estimated 1RM. Thus, the 10RM protocol will be performed for all exercises with free weights [56] and will be re-evaluated after 8 weeks to guarantee that the exercise prescription is continuously updated. As a complementary method, the intensity will also be monitored through the rate of perceived exertion (RPE) using a reliable and valid tool [63] − Borg CR-10 scale [64]. This scale will be presented at the end of each session, in which the participants record their RPE (range from level 1 to 10, extremely easy and extremely hard, respectively) [64].

### Adverse events

Despite all the safety procedures established to ensure the safety of the participants (e.g., exclude those with significant risk in participating; control and measurement of training intensity), unforeseen adverse events may occur. An adverse event represents an untoward medical problem during the study, which may or may not be caused by the exercise program or the assessments [46]. Exercise instructors will monitor adverse events, asking the participants if they have experienced any health problems (e.g., physical injuries, muscle soreness) since the last session [58]. All adverse events that may occur during the participation in this study will be monitored and analysed by the research team.

### Blinding (masking)

Given the nature of this program, neither participants nor PI can be blinded to allocation but are clearly instructed to not reveal the allocation status at the follow-up assessments [46]. To minimize the risk of bias, we will adopt the following methods. The randomization process will be generated by an independent biostatistician using a computer-generated list of random numbers. Participants will be enrolled and assigned to their intervention groups by the PI. The assessments will be organized by the PI and will be applied by invited specialists and co-investigators of the research team, which will be blinded to allocation. The two instructors of the CT exercise program will not take part of the data collection. To minimize differences in the procedures, the same testing staff will perform data collection in the different assessment moments (pre-, mid- and post-testing). Data will be entered and organized electronically into the database by an independent researcher outside the research team. All participant information will be coded, and the code will be stored in a locked local and only the PI will have key access. This procedure assures that both outcomes assessor and data analyst will not have access to information about the allocation of participants [46].

### Outcome measures

This trial includes a screening and baseline assessment period of 20 days (four visits), a 16-week CT program period, and a mid-testing and post-testing period of 3 (one visit) and 10 days (two visits), respectively. On the first visit, subjects will sign the informed consent form and will complete additional screening measures. Subjects that meet all eligibility criteria will be enrolled and complete a set of outcome measures over visits 2 and 3. After the baseline assessments, subjects will be randomly assigned to either control or experimental group, and the participants of the experimental group will carry out the evaluations of 10RM (Visit 4). The exercise sessions will be performed over 16-weeks on a single site and supervised by two instructors. Baseline assessments will be repeated after 8 weeks (mid-testing, visit 5) and upon completion of the intervention (visits 6 and 7). Importantly, we will consider the phase of the menstrual cycle in non-menopausal women (i.e., menstrual phase, follicular phase, ovulation phase and luteal phase), taking baseline and follow-up evaluations at the same time of the cycle. A timetable of the enrolment, intervention and assessments are presented in Table 3.

**Table 3 pone.0263455.t003:** Schedule of enrolment, interventions, and assessments.

	STUDY PERIOD							
	Baseline				Intervention	Follow-ups		
Timepoint	Visit 1^a^	Visit 2^a^	Visit 3^a^	Visit 4^a^	Sessions 1–48^b^	Visit 5^c^	Visit 6^d^	Visit 7^d^
Day number	-20 to -15	-15 to -10	-10 to -5	-5 to -1	1 to 112	56 to 58	113 to 118	118 to 123
**SCREENING/BASELINE**								
Informed consent, review inclusion/exclusion criteria	x							
Sociodemographic information	x							
Medical history	x							
Body mass index measurement	x							
**INTERVENTIONS**								
Combined training group					x			
Control group					x			
**ASSESSMENTS**								
Fasting blood samples		x					x	
Saliva samples		x					x	
Body composition			x			x		x
Physical fitness			x			x		x
Lung function (Spirometry)			x			x		x
Subjective quality of life			x			x		x
Systolic and diastolic blood pressure	x		x			x		x
Assessment of dietary intake			x					x
Accelerometry		x					x	
**RANDOMIZATION**				x				
Maximal dynamic strength to estimated 1RM				x		x		

^a^ Screen and baseline assessments will be completed within 20 days;

^b^ The exercise sessions will be performed 3 times/week (i.e., Monday, Wednesday, and Friday) over 16 weeks;

^c^ This study includes an intermediate assessment, which will be carried out in the eighth week of intervention;

^d^ Post-testing assessments will be done within 10 days of the last exercise session.

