*Brachial blood pressure*. The right and left brachial systolic blood pressure (SBP) and diastolic blood pressure (DBP) will be measure using an automated oscillometric cuff (OMRON, HEM 907, Japan). The participant will be comfortably seated, with the legs uncrossed and the back and arm supported, for 3–5 minutes without speaking and/or moving before recording the first measure [69, 70]. Two readings will be taken at intervals of at least 1–2 minutes and the average of those readings will be recorded as the participant’s BP. However, if the values deviate by ≥ 5 mmHg, a third measurement will be performed, and the average of these multiple readings will be used [69, 70]. The participants must avoid caffeine, physical exercise, and smoking for at least 30 minutes prior to measurement [69]. The brachial BP will be assessed in the morning (between 09:00h – 12:00h) and will be performed by a doctor.

*Lung function*. Spirometry will be conducted using the Spiropalm 6MWT (Cosmed, Italy) Spirometer. Participants will perform a maximal inspiratory and expiratory maneuver to achieve the Forced Vital Capacity (FVC), Forced Expiratory Volume in 1 second (FEV_1_), and Peak Expiratory Flow (PEF). Participants’ data will be classified to indicate repeatability. In this sense, the participants will have to complete at least three acceptable FVC maneuvers to be included in the analysis (i.e., the difference between the best two FEV_1_ and FVC values must be within 150 mL) [71, 72]. The best FEV_1_ and best FVC measures of the participants will be recorded and used for data analysis, according to procedures adopted in other studies [20, 21]. Predicted FEV_1_ (FEV_1_% pred), predicted FVC (FVC% pred), and predicted PFE (PFE% pred) will be calculated based on age, stature, ethnicity, and sex using the formulas developed by the Global Lung Function Initiative [73]. The lung function assessment will occur in the morning (between 09:00h – 12:00h) and will be performed by a doctor.

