### Data analysis

Data analyses will be performed using SPSS Statistics version 25.0 (SPSS Inc., IBM Company, Chicago, Illinois, USA). Descriptive statistics (mean ± SD) will be performed for all variables in the analysis. The assumption of normality will be tested using histograms, normal probability plots and Shapiro-Wilk test. Chi-squared test will be performed to analyse sex proportions between groups. Assuming data normality, a two-way analysis of variance (ANOVA) for repeated measures will be applied for intra- and inter-group comparisons. In absence of normality, non-parametric Kruskall-Wallis test will be used. Bonferroni’s *post hoc* test will be performed if significant differences exist (alpha level set at 0.05). The magnitude of the global effect size will be calculated using Cohen’s effect size [104]. The Cohen’s d effect size is categorized according to the following criteria: *d* = < 0.20 (small), 0.21–0.79 (medium) and > 0.80 (large) [104]. The bivariate associations between the changes promoted by the exercise program and the different variables studied will be assessed by Spearman’s rank and Pearson’s coefficients. The strength of the associations will be classified as follows [105]: very high (0.90 < r < 1.00); high (0.70 < r < 0.90); moderate (0.50 < r < 0.70); low (0.30 < r < 0.50); little (0.10 < r < 0.30). Significance level set at *p* ≤ 0.05.

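### Blood pressure is read at two visits before randomisation; entering both readings as covariates would be an optional gain in precision for that outcome

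*Protocol article*

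**What the plan says.** Table 3 of the protocol article, in its assessments block, marks "Systolic and diastolic blood pressure" at Visits 1, 3, 5 and 7. Randomisation is marked at Visit 4, and the text agrees: "After the baseline assessments, subjects will be randomly assigned to either control or experimental group". Visits 1 and 3 therefore both precede allocation.

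Outcome measures describes Visit 1 as a screening visit: "On the first visit, subjects will sign the informed consent form and will complete additional screening measures". Eligible subjects then "complete a set of outcome measures over visits 2 and 3". A screening pressure is needed because Table 1 excludes "Uncontrolled or abnormal blood pressure".

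The measurement method stands under Primary outcomes: "The right and left brachial systolic blood pressure (SBP) and diastolic blood pressure (DBP) will be measure". Two readings are taken a minute or two apart, and "the average of those readings will be recorded as" the participant's value, with a third reading if they disagree. This averages within a visit only. Blood pressure is not named in the lists of primary outcomes in the Abstract or at the end of the Introduction.

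Under Data analysis, "a two-way analysis of variance (ANOVA) for repeated measures will be applied for intra- and inter-group comparisons". That section does not define the baseline for blood pressure.

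**The concern.** Averaging readings taken minutes apart does not remove day-to-day variation in blood pressure. A reading on another day does help, and the trial already collects one. If baseline is Visit 3 alone, the day-to-day variation of that single visit goes straight into each participant's change and so into the comparison of arms.

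What is at stake is precision on one outcome in a trial of 20 per group. Both readings precede allocation, so treatment cannot affect either, and using both would need no new measurement.

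**Working it through.** **The plan's own figure.** Estimated sample size gives effect size 0.30, 5% alpha, 95% power and 20 per group. Read as a within-between interaction in a repeated-measures ANOVA with 2 groups, and assuming 2 measurements and correlation 0.5 (neither is stated), the noncentrality is 0.30² × 40 × 2 / (1 − 0.5) = 14.4 on 1 and 38 degrees of freedom. Power is 0.959 and the minimum total is 40. The figure reproduces and does not depend on how baseline blood pressure is defined.

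**Inputs for the comparison.** The documents give no SD or between-visit correlation. Assume equal SDs (set to 1). Write c for the correlation of Visit 1 with Visit 3, a for Visit 1 with follow-up and b for Visit 3 with follow-up. Total N = 40.

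**Formulas, for one follow-up visit.**
- Change from Visit 3: 2(1 − b).
- Adjusted for Visit 3: 1 − b².
- Adjusted for both visits as separate covariates: 1 − (a² + b² − 2abc)/(1 − c²).
- Change from the simple mean: 1 + (1 + c)/2 − (a + b).
- Adjusted for the simple mean: 1 − [(a + b)/2]² / [(1 + c)/2].

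Estimating q covariate slopes multiplies the variance of the adjusted difference by about 1 + q/(N − q − 3). That is 37/36 for one covariate and 37/35 for two, so the second covariate costs a factor of 36/35, about 3%. Change scores carry no such factor.

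**Two separate covariates.** The last two columns include the small-sample factors.

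| c, a, b | Change | Visit 3 adjusted | Both adjusted | Both v change | Both v Visit 3 adjusted |
|---|---|---|---|---|---|
| 0.5, 0.5, 0.5 | 1.000 | 0.750 | 0.667 | 0.70 | 0.91 |
| 0.7, 0.7, 0.7 | 0.600 | 0.510 | 0.424 | 0.75 | 0.85 |
| 0.8, 0.8, 0.8 | 0.400 | 0.360 | 0.289 | 0.76 | 0.83 |
| 0.7, 0.6, 0.7 | 0.600 | 0.510 | 0.486 | 0.86 | 0.98 |
| 0.6, 0.5, 0.7 | 0.600 | 0.510 | 0.500 | 0.88 | 1.01 |

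Example, last row: (0.25 + 0.49 − 0.42)/0.64 = 0.50, leaving 0.50. Then 0.50 × (37/35)/0.60 = 0.88, and (0.50/0.51) × (36/35) = 1.01.

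The closed form thus gives 12% to 30% against change. Simulation at 20 per arm, with and without truncation at Visit 1, gave about 12% to 31% against change, and between break-even and 18% against Visit 3 adjustment.

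**The simple mean.** When all correlations equal r, the change variance falls from 2(1 − r) to 1.5(1 − r), a ratio of 0.75 whatever r is. That result needs the two visits to be exchangeable. With 0.7, 0.6, 0.7 the ratios are 0.55/0.60 = 0.92 for change and 0.503/0.510 = 0.99 with adjustment. With 0.6, 0.5, 0.7 they are 0.60/0.60 = 1.00 and 0.55/0.51 = 1.08: no gain for change, and an 8% loss with adjustment.

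**The case against.** The strongest reply is that nothing here is wrong. The article does not define baseline blood pressure and nowhere says that Visit 1 is dropped. Such a definition is commonly left to the analysis plan, which is not shown. This stands, and it is why the point is an optional improvement. A reader might infer that the protocol throws away a primary-outcome baseline; the documents only imply Visit 3.

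The second reply is that Visit 1 is not a duplicate of Visit 3. It serves an exclusion criterion, so its range may be restricted. The rule under Blinding that the same staff collect data names pre-, mid- and post-testing but not screening. By Table 3, Visit 1 (days −20 to −15) and Visit 3 (days −10 to −5) lie 5 to 15 days apart, while Outcome measures wants baseline and follow-up at the same point of the menstrual cycle in non-menopausal women. All this stands against a simple mean, and against the tempting claim of a free 25% at any correlation. It does not defeat two separate covariates, because the fitted slopes give a weaker Visit 1 reading less weight.

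Third, a two-visit mean placed in the repeated-measures ANOVA would have a smaller variance than the single-visit follow-ups. With a common correlation r, its difference from a follow-up has variance 1.5(1 − r), against 2(1 − r) between Visits 5 and 7, which breaks sphericity. That also stands against the mean. Covariates avoid it, but they do replace the stated model for this outcome.

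**Conclusion.** The point holds as an optional precision improvement for systolic and diastolic pressure. Using both pre-randomisation readings as separate covariates lowers the variance of the between-arm difference by roughly 12% to 31% against the planned change contrast. Against a model already adjusted for Visit 3 it is about 0% to 18% lower. So part of the larger range comes from baseline adjustment itself, and the rest from the second reading.

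These ranges rest on equal SDs, assumed correlations of 0.5 to 0.8, 20 per arm and one follow-up visit at a time. The three-visit omnibus ANOVA test was not computed. If Visit 1 tracked follow-up more weakly still (0.5, 0.4, 0.7), both-adjusted variance would be 0.507. That is 11% below change (0.507 × 37/35 / 0.60 = 0.89), but about 2% above Visit 3 adjustment (0.507/0.510 × 36/35 = 1.02).

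A reader might go on to infer bias or an inadequate sample size. Neither follows. Both readings precede allocation, so the randomised comparison is unbiased with either, and the sample size is not tied to blood pressure. Nor is this clearly a headline outcome: it is described under the Primary outcomes heading but is absent from the primary-outcome lists in the Abstract and Introduction.

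**What to change.** Before outcome data are seen, state for systolic and diastolic pressure that the arms will be compared at Visits 5 and 7 in a baseline-adjusted model with the Visit 1 and Visit 3 values as two separate covariates. Do not prescribe their simple mean. Base inference on the between-arm difference and not on change within an arm, because screening on blood pressure at Visit 1 can distort within-arm change through regression to the mean.

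The cost is one residual degree of freedom for the second reading, about 3% in variance at this size, and a covariate-adjusted model in place of the stated ANOVA for this outcome. No new measurement is needed. If the team prefers Visit 3 alone, a sentence naming it as the baseline would remove the ambiguity.
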